\begin{document} m = \frac{(Z_{1-\alpha/2} + Z_{1-\beta})^2 \, 2\sigma^2}{\Delta^2} \left[ 1 + (n - 1)\rho \right] \end{document}

where *m* is the number of households per arm; *Z_1−α/2_* is the standard error associated with a 95% confidence interval (*Z_1−α/2_*=1.96); *Z_1−β_* is the standard error associated with 80% power (*Z_1−β_*=0.842); Δ is the mean awareness score difference between the pre- and post-assessments in the intervention group within a community-based trial on disaster preparedness intervention (Δ=15.97) [26]; σ^2^ is the total variation in awareness score between the pre- and post-assessments in the intervention group within the same trial (σ^2^=138.949) [26]; *n* is the estimated median number of households in Proto-Malay majority Orang Asli villages in Selangor (*n*=54) [18]; and ρ is the intracluster correlation coefficient (ICC) (ρ=0.048) [27].

Allowing for an anticipated attrition rate of approximately 30%, the ideal sample size was set at 45 households per arm. Following the CONSORT Statement recommendation that each study arm should include at least four clusters [28], this study employs multistage sampling to select four Orang Asli villages per arm, aiming for 12 households in each village, a total of 96 households for the study.

Eligibility criteria

Table 2 outlines the eligibility criteria for clusters at both the district and village levels. Meanwhile, Table 3 provides the inclusion and exclusion criteria for participants who will represent their households by participating in X-SIAGA and completing a questionnaire designed to assess the change in preparedness scores at all data collection points.

**Table 2 TAB2:** Eligibility criteria for district and village level clusters.

District	Village
Districts in the state of Selangor.	Villages that have not previously participated in any outbreak preparedness programs.
Districts with gazetted Orang Asli villages.	Villages with more than 12 households.
Districts with more than 5 Orang Asli villages.	Villages accessible via road transport.

**Table 3 TAB3:** Inclusion and exclusion criteria of participants.

Inclusion criteria	Exclusion criteria
Orang Asli descent.	Having physical or cognitive disabilities (e.g., blindness, deafness, schizophrenia and dementia).

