Each household will also receive a booklet that includes the materials covered during the X-SIAGA program. Participants start using the booklet during the program, and they take it home for self-study with other family members and to complete their household outbreak preparedness plans. Additionally, they will receive a set of the “Wabak X” card game and are encouraged to play it with their family members. The pair of adults representing their household will complete a questionnaire to assess the change in preparedness scores at all data collection points.

This study aims to assess the effectiveness of X-SIAGA under realistic conditions. This means there will be no refresher sessions or reminders. Instead, only follow-ups at specific time points for data collection will occur. This approach is designed to mirror real-world conditions, as health promotion programs conducted by various local agencies, including government ministries and community organizations, are typically held only once or at most twice per year.

Control

In the control group, households from four Orang Asli villages receive only educational brochures on communicable disease prevention, without the X-SIAGA intervention package. These brochures, sourced from the District Health Office, are currently used by the public health promotion team for education on awareness and prevention of infectious diseases and outbreaks in local communities. Similarly, two eligible adults from each control group household will participate in the research activities and complete the questionnaire at all data collection points. The control group will receive the X-SIAGA intervention package after data collection for all participants is completed.

Data collection

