To prevent contamination bias, the study ensures sufficient geographical separation between intervention and control villages to minimize interactions among participants from different groups. Prior to recruitment, the research team held meetings with village leaders and committee members, in the presence of JAKOA officials, to explain the X-SIAGA intervention, emphasize the importance of strict confidentiality, and discourage discussions about the intervention. These leaders and committee members then conveyed this information to eligible participants during household recruitment. All participants will again receive a detailed explanation of the privacy and confidentiality policy when expressing interest in joining the trial, and only those who provide consent will be enrolled. To mitigate attrition bias, the study will employ an Intention-to-Treat (ITT) approach. Additionally, to sustain motivation and engagement, perishable goods will be offered as incentives at each stage of data collection.

Statistical methods

The statistical analysis for this study will be carried out by using the IBM SPSS Statistics for Windows, Version 26 (Released 2018; IBM Corp., Armonk, New York). Descriptive statistics will include frequency and percentages for categorical data and mean and standard deviation for numerical data.

To compare baseline sociodemographic characteristics between the intervention and control groups, a Pearson Chi-Square test will be utilized for categorical variables, while an Independent Samples t-test will be used for continuous variables. To evaluate changes over time from T0 to T3 between and within the groups, a repeated-measures analysis of variance will be conducted. To assess variation in results between and within the groups across the different time points, while also controlling for potential confounding variables, a generalized estimating equation will be utilized.

Statistical analyses will use a two-tailed test to evaluate the superiority hypothesis. The null hypothesis states that there is no difference between the X-SIAGA intervention package and standard educational brochures. A significance level of 0.05 will be applied.

Data management

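### The repeated-measures ANOVA named for between-group change takes no account of the eight randomised villages, so its between-group tests do not reliably hold the 0.05 level

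*Protocol article*

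**What the plan says.** Under Sampling, randomization, allocation, and blinding, the protocol article draws two districts and four villages in each, and allocates two villages to intervention and two to control within each district. The village is therefore the randomised unit, with four per arm. Under Sample size, the formula carries a design-effect term with an "intracluster correlation coefficient (ICC") of 0.048, so the authors expect scores to be correlated within villages.

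The Statistical methods section then names the outcome analyses. The first is: "To evaluate changes over time from T0 to T3 between and within the groups, a repeated-measures analysis of variance will be conducted". The second looks at variation between and within groups across time points, "while also controlling for potential confounding variables, a generalized estimating equation will be utilized". On testing it adds: "Statistical analyses will use a two-tailed test to evaluate the superiority hypothesis" and "A significance level of 0.05 will be applied". Neither method is given a village term, a cluster variable or cluster-level degrees of freedom, and neither is labelled the primary analysis.

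On respondents, the Intervention section says: "The pair of adults representing their household will complete a questionnaire". The Outcome measures section defines the score, and the preparedness category derived from it, at household level.

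**The concern.** The sample size allows for village clustering and the named ANOVA then leaves it out. A repeated-measures ANOVA removes the correlation between visits of the same unit. It has no random effect for village, so its between-group error term is the variation between households, not between villages.

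If households in a village resemble each other, that error term is too small. Confidence intervals for the group difference come out too narrow and p-values too small, for the primary score and for both secondary scores. With only four villages per arm, a nominally significant difference could reflect which villages fell in which arm.

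**Working it through.** **Inputs from the protocol.** Two-sided alpha 0.05 (Statistical methods); Δ = 15.97, σ² = 138.949, formula cluster size 54, ICC 0.048, four villages per arm, 12 households per village, about 30% attrition (all Sample size); four visits, T0 to T3 (Data collection).

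**The plan's own figure.** m = (1.96 + 0.842)² × 2 × 138.949 / 15.97² × [1 + 53 × 0.048] = 8.555 × 3.544 = 30.3. This reproduces the stated 30 households per arm and confirms that clustering was allowed for at the design stage.

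**1. Test of a single score, ignoring village.**
- Design effect DE = 1 + (12 − 1) × 0.048 = 1.528.
- True alpha = 2 × [1 − Φ(1.96/√1.528)] = 11.3%.
- With 8.4 households per village after 30% attrition, DE = 1 + 7.4 × 0.048 = 1.355 and alpha is 9.2%.
- For an assumed ICC of 0.01 to 0.10 at 12 per village, alpha is 6.3% to 17.6%.

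**2. ANOVA group effect, averaged over four visits.** Two quantities must be assumed. The first is a stable household share of the total variance, taken as 0.45, which leaves a residual share of 1 − 0.048 − 0.45 = 0.502. The second is s, the fraction of the village variance that changes from visit to visit.
- Village variance of the four-visit mean: 0.048 × (1 − s) + 0.048 × s/4.
- Household variance of that mean: 0.45 + 0.502/4 = 0.5755.
- s = 0: ICC of the mean = 0.048/0.6235 = 0.077, DE = 1.847, alpha = 14.9%.
- s = 1: ICC of the mean = 0.012/0.5875 = 0.0204, DE = 1.225, alpha = 7.6%.

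Simulation (8 villages × 12 households × 4 visits, 8,000 null runs) gave 14.8% and 7.4%.

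**3. ANOVA group-by-time test.** A constant village effect cancels from this test; only the part that varies by visit matters. The expected mean square for the interaction is 0.502 + 12 × 0.048 × s. For the ANOVA error term it is 0.502 + (36/47) × 0.048 × s, because 48 households per arm contain four villages. With R the ratio of the two, the true alpha is approximately the probability that F on 3 and 282 df exceeds 2.637/R.

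| s | R | alpha, formula | alpha, simulated |
|---|---|---|---|
| 0 | 1.000 | 5.0% | 5.3% |
| 0.25 | 1.264 | 10.2% | 10.5% |
| 0.50 | 1.518 | 16.0% | 16.8% |
| 1 | 2.001 | 26.9% | 26.4% |

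**4. GEE, by cluster unit.** Clustered on household, it ignores village just as the ANOVA does; simulated alpha for the group effect was about 8% to 16%. Clustered on village, with the ordinary sandwich variance and a normal reference, alpha with 4 + 4 equal clusters is 2 × P(t on 6 df > 1.96 × √(3/4) = 1.697) = 14.1%, whatever the ICC. Actual fits (800 null runs) gave 16.5%; with a bias-reduced variance and a t reference on 6 df they gave 4.0%.

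**5. Village-level test.** A t-test on village-mean change (6 df, critical value 2.447) gave 4.5% to 5.2% in the simulations of steps 2 and 3, whatever s was.

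**6. Power of that test on the plan's own figures.** SE = √(2 × 138.949 × DE/(4m)). At m = 12, SE = 2.974 and Δ/SE = 5.37, which gives 99% power on 6 df. At m = 8.4, SE = 3.348 and Δ/SE = 4.77, which gives 97.5% on 6 df, 96.3% on 5 and 93.8% on 4. These use the protocol's Δ, which is a pre-post awareness difference from another trial, as if it were the between-arm difference.

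**The case against.** The strongest reply is that the quoted sentence concerns change over time. Its natural test is therefore group-by-time, from which a stable village effect cancels. This is correct as far as it goes: with constant village effects that test holds about 5%, and the 11% figure belongs to a different test. It does not rescue the plan, because constancy is an assumption the protocol neither states nor supports. The intervention is a one-day group session run in each village, and village committee representatives may help with the questionnaires. Both can make village effects differ by visit.

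A second reply is that this is a condensed article and a statistical analysis plan may settle the GEE details. That stands. A reader might infer that the GEE will be run with an uncorrected variance, but the protocol says nothing about its cluster unit, variance or reference distribution. The 14% figure is what would follow from one particular choice. The reply does not cover the ANOVA, which is a stated choice and not an omission.

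Two other stronger readings are tempting. One is that these are the designated primary analyses. The protocol labels neither so; they are simply the outcome analyses it names. The other is that the two adults of a household enter as independent rows, which would put alpha at about 20% to 24% for an assumed within-household correlation of 0.3 to 0.7. The text does not say whether the pair yields one form or two, and it defines the score per household. That figure is not part of this point.

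**Conclusion.** The point holds for the repeated-measures ANOVA. It is named for between-group change in a village-randomised trial whose own sample size assumes an ICC of 0.048, and it ignores village. At that ICC and 12 households per village, the true alpha is about 11% for a single score and about 7% to 15% for the group effect over visits. For group-by-time it runs from about 5% to about 27%.

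The single-score figure rests on the protocol's numbers alone. The other two also depend on an assumed household variance share of about 0.45 and on the share of village variance that changes by visit, which the documents do not give. It therefore cannot be said that every test from this ANOVA is inflated, only that none is protected by design. For the GEE, the conclusion is conditional on how it is specified.

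**What to change.** Drop the repeated-measures ANOVA as a test of the intervention effect. Use one score per household per visit and test the effect at village level, in one of two ways:

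- a t-test on village-mean change from T0 to the chosen follow-up visit, on 6 df, or 5 df with district in the model; or
- a mixed model for the follow-up scores with arm, time, arm-by-time, district and baseline score as fixed effects, random effects for village, village-by-time and household, and Satterthwaite or Kenward-Roger degrees of freedom.

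The village-by-time term is essential. With random intercepts for village and household only, the arm-by-time F in balanced data equals the ANOVA's F and is no better protected.

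If GEE is kept, make village the cluster and use a small-sample-corrected variance with a t reference. A permutation test is not a substitute: two of four villages per district gives 6 × 6 = 36 allocations, so the smallest two-sided p is 2/36 = 0.056.

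The cost is a change of wording and no new data. Confidence intervals become wider and degrees of freedom are few. Adjusting eight village means for both district and baseline leaves 4 df (critical value 2.776, against 2.447 on 6 df). On the protocol's own Δ, variance and ICC, power stays above 90% after 30% attrition.

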## Results

Results are not yet available at this stage. Data will be compiled in Microsoft Excel (Microsoft Corporation, Redmond, Washington) and analyzed using IBM SPSS as outlined in the Materials and Methods section. The analysis and reporting of results are planned upon study completion. The results of the study will be reported in accordance with the Consolidated Standards of Reporting Trials (CONSORT) statement [28]. It is anticipated that the intervention will lead to improved preparedness levels among participating households.

## Discussion

This study will be a two-arm cluster randomized trial evaluating the effectiveness of the X-SIAGA intervention. The X-SIAGA intervention is a novel, theory-based intervention package tailored for the Orang Asli community to enhance their household preparedness for Disease X and future outbreaks. This intervention aims to empower the community to respond effectively to infectious disease outbreaks, including novel threats, while waiting for intervention from health authorities, thereby reducing the negative impact and mortality rates associated with such events.

X-SIAGA addresses a crucial gap in micro-level preparedness. While numerous initiatives focus on macro-level preparedness, outbreaks invariably begin and spread within communities before being detected by authorities. Marginalized populations, such as Indigenous communities, are often disproportionately affected due to pre-existing vulnerabilities and limited access to resources [17,19]. Most existing community preparedness programs in Malaysia target floods, with no known initiatives addressing outbreak preparedness at the household level, especially among the Orang Asli [9]. X-SIAGA is pioneering as the first outbreak preparedness program in Malaysia tailored to the needs of the Orang Asli.

The study’s findings are anticipated to provide essential insights and evidence for the development of targeted health interventions, significantly contributing to enhancing public health preparedness and resilience, especially within marginalized communities.

While X-SIAGA has its strengths, there are notable limitations to the study. The expectation of immediate personal benefits among the Orang Asli population may pose challenges in participant recruitment and retention. The potential Hawthorne effect cannot be fully dismissed; mitigation efforts will include assuring participants that responses will not incur any penalties.

The X-SIAGA intervention will be conducted in a single session, with a follow-up period restricted to three months due to resource and time constraints. While some studies have shown that community interventions delivered in one session can lead to beneficial outcomes in a short timeframe [29,30], expecting sustained change from a single session may not be realistic, and short-term follow-ups might overlook the long-term effects of the intervention.

The generalizability of the findings might be limited due to the unique aspects of the Orang Asli community in Malaysia. The Orang Asli community in Selangor may also not be representative of Orang Asli tribes from other states, as some can be very different from one another. Furthermore, nonrandom household recruitment could lead to homogeneous views within social networks, and individuals holding village roles or being more vocal might disproportionately influence the study’s findings.

## Conclusions

This protocol outlines X-SIAGA, an intervention package designed to enhance preparedness for Disease X and potential outbreaks among Orang Asli households in Selangor. By comparing X-SIAGA with conventional educational brochures, the study aims to determine whether this comprehensive, tailored, and evidence-based intervention provides measurable benefits. If proven effective, X-SIAGA could be proposed for wider implementation and adapted for use in other communities.
